#### - Surgical procedure in EDB group

If the patient is allocated to the EDB-group, the clip is closed. The size and numbers of clips used will be determined intraoperatively (Weck Horizon, size 'micro' to 'wide, Teleflex). The titanium clips are applied by using a clip applicator (Weck Horizon) and a McGee bending forceps (Aesculap).

Theoretically, it is possible that the endolymphatic duct cannot be identified. In that case, the endolymphatic sac is separated from the posterior canal to ensure an arrest of the flow of endolymphatic fluid between the inner ear structures and the endolymphatic sac. This is done by placing a barrier of autologous temporal fascia glued with Tisseel. This way, the same result as blockage with a clip is obtained.

In the case of tearing of the dura leading to liquor leakage, this will be treated with tisseel, fascie and novacol. The cortex is not restored. The skin is closed in a regular way.

#### - Surgical procedure in endolymphatic sac decompression (control) group

The same surgical procedure is carried out in the decompression group. After identification of the endolymphatic duct, a CT scan is performed to assess if the endolymphatic duct was identified correctly. After ensuring the structure is indeed the duct, it is decompressed. In this group too, the cortex is not restored.

## **5.2 Use of co-intervention**

Every patient will be treated by an experienced and skilled vestibular therapist after surgical intervention. The vestibular therapist will perform a functional assessment (including DGI, DVAT-NI, Romberg, sharpened Romberg, One Leg Stance Test and Motion Sensitivity Test) preoperatively. Based on the results, an individual tailored program will be made by the physiotherapist and the intensity of vestibular rehabilitation will be determined.

The program addresses patient functional deficits like visual, balance, gait and habituation disorders. Five 30-minute-sessions of vestibular rehabilitation will be given over a 3 months period. Training consists of habituation exercises (based on the Motion Sensitivity Test, developed by Shepard & Telian 1990), gaze stabilization exercises (according to Herdman 2014), postural stabilization exercises (balance training according to the framework of Klatt et al (2015)) and gait training according to the framework of Klatt et al. (2015) and Clendaniel, Tucci (1997). Apart from the sessions with the vestibular therapist, the patient must perform habituation and gaze stabilization exercises 2-3 times a day. Moreover, postural stabilization exercise and gait training must be performed 2-3 times a week.

If a patient has an increased risk of anxiety problems (HADS > 7), a written explanation will be given containing psychoeducation and advice of behaviour change based on cognitive-behaviour theory and self-regulation theory (according to Yardley and Kirby 2006).

The full vestibular rehabilitation treatment protocol can be found in the appendix (Appendix 3).

## **5.3 Escape medication**

Medical indications or international guidelines about intervention after surgery are lacking. The decision to start any co-intervention will be based on the participants' experience of vertigo attack frequency and patient-doctor preference (shared decision-making). Shared decision-making ensures wide applicability of study results and reflects daily medical practice. The protocol for frequency and methods of IT injections can be found in the appendix (Appendix 4).

The use of metoclopramide in an acute phase of vertigo is allowed. The following dosages will be prescribed:

- Metoclopramide oral or rectal with a maximum of 30 mg per 24 hours  
and/or
- Betahistin with a maximum of 48 mg per 24 hours or cinnerrazine with a maximum of 75 mg per 24 hours  
and/or
- Ondansetron with a maximum of 16 mg per 24 hours

Moreover, intervention may be carried out after surgery if the patient continues to suffer from vertigo attacks. This may be intratympanic injections of corticosteroids or in exceptional cases, ablative surgery such as vestibular neurectomy and labyrinthectomy. This is offered when the bouts of vertigo are intolerably frequent.

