### - Epidemiology

Few articles have been published on the epidemiology of MD. Great variation exists in the published reports of the prevalence of MD, ranging from 34.5 cases per 100,000 population in Japan (Shojaku 2005) to 46 cases per 100,000 population in Sweden (Stahle 1978). In the United States of America, reported prevalence is much higher: Alexander (Alexander 2010) reports 190 patients per 100,000, Waldislavosky-Waserman (Wladislavosky-Waserman 1984) reports a prevalence of 218 per 100.000. The difference in prevalence might be due to the wide variations in definitions of MD.

In the Netherlands, a population of 60-100 per 100,000 patients is severely impaired (defined as low quality of live) by the disease (Mateijsen, 2001). There seems to be a slight female preponderance, with up to 1.3 times more women affected than men. The disease is more common in adults in their fourth and fifth decade of life (Kotimaki 1999, Perez 2008, Van Esch 2016).

- Current treatment options and guidelines

The treatment of MD both in primary and secondary care setting is focused on the reduction of the frequency and intensity of vertigo attacks. Current treatments have either proven to be ineffective (Betahistin; Adrion 2016), only have a temporary effect (intratympanic dexamethasone injections; McRackan 2014, or methylprednisolone; Patel 2016), or destroy the labyrinth function (intratympanic gentamicin, labyrinthectomy, selective neurectomy; Pullens 2013; Harner 2001, Sennaroglu 2001). Surgical destruction of the labyrinth reduces the episodes of attacks but causes loss of balance as well, due to one dysfunctional labyrinth. Moreover, permanent hearing loss is reported after this treatment.

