## 10. STATISTICAL ANALYSIS

Statistical Data analysis of the study data will be performed using SPSS (version 17.0). All analyses will be performed through Intention to treat.

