### 10.1 Primary study parameter

The primary outcome is defined as being attack free at 12 months follow-up. The required significance level of findings ( $\alpha$ ) will be equal to or lower than 5%. Any statistical tests will be two-sided. P-values will be presented. Where confidence limits can be estimated, the confidence level will be 95%. All analyses will be performed by intention to treat.

A chi-square test (or Fisher's exact test) will be performed on the primary outcome variable data (number of patients free of vertigo attacks at 12 months post-operatively, in EDB vs endolymphatic sac decompression group).

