#### **10.1.2 Computation of outcome**

The outcome will be determined from the imputed App-data. It is expected that attacks are reported reliably and missing data can be reliably imputed as being attack free. In principle, a patient can be sometimes imputed as having an attack on otherwise as being attack-free. To account for these potential cases, a cut-off of 10% for the attack probability (as the imputed frequency for having an attack) will be used to determine presence/absence of attacks.

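### The primary outcome ignores rescue, so on the natural reading a participant made attack free by later ablative surgery is scored as a success of the assigned operation

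*Protocol*

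**What the plan says.** Protocol 10.1 sets the endpoint: "The primary outcome is defined as being attack free at 12 months follow-up". Section 8.1.1 gives the same parameter as a count of patients. Section 10.1.2 names the data source: "The outcome will be determined from the imputed App-data". Chapter 10 adds "All analyses will be performed through Intention to treat", and 10.1 repeats it.

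Section 5.3 states that "intervention may be carried out after surgery if the patient continues to suffer from vertigo attacks", and then lists the options: "This may be intratympanic injections of corticosteroids or in exceptional cases, ablative surgery such as vestibular neurectomy and labyrinthectomy". The decision is shared and not standardised: "The decision to start any co-intervention will be based on the participants' experience of vertigo attack frequency and patient-doctor preference".

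Section 8.1.2 counts ablative surgery as a secondary parameter (co-interventions) and intratympanic injections as another (escape medication). Neither 8.1.1 nor 10.1 links these to the primary outcome. The only analyses that score participants as failures or successes by rule are the two sensitivity analyses in 4.4, and those concern missing outcomes.

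Chapter 1 describes what ablation does: "Surgical destruction of the labyrinth reduces the episodes of attacks but causes loss of balance as well". It presents EDB as a technique that leaves the inner ear's function intact.

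**The concern.** Rescue is triggered by continuing attacks, that is, by failure of the assigned operation to control vertigo. An endpoint built only from attack reports around month 12 cannot tell a participant controlled by the study operation from one controlled by a later labyrinthectomy or neurectomy. Both are attack free.

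That conflicts with the trial's purpose. The objective is to compare two function-preserving operations, and the protocol's case for EDB rests partly on avoiding destruction of the labyrinth. Crediting decompression (or EDB) with the result of an ablation answers a different question.

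It also matters for power. If decompression fails more often than EDB, as the sample size assumes, more decompression participants are open to rescue and the observed difference shrinks.

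**Working it through.** **Inputs.** From 4.4: planned success 95% (EDB) and 70% (decompression), two-sided 5%, 32 per arm required for Fisher's exact test, plus 5 per arm for loss, giving 37 per arm and 74 in total. From 10.1: chi-square or Fisher's exact test. Not in the protocol: f, the share of failures that rescue makes attack free by month 12. It is treated below as an assumption over a range.

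**The plan's own figure.** Exact binomial enumeration at 32 per arm, 95% v 70%, gives power of 81% for the uncorrected (Pearson) chi-square test and 68% for two-sided Fisher. So 32 fits the chi-square test but not Fisher, the test named in 4.4. The step 32 + 5 = 37 reproduces. At 37 per arm, power is 86% (Pearson) and 78% (Fisher). These are the f = 0 reference values.

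**Candidates for rescue, per 37.**
- Decompression: 0.30 x 37 = 11.1
- EDB: 0.05 x 37 = 1.85
- Ratio: 0.30 / 0.05 = 6

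**Effect on the contrast.** With the same f in both arms:
- EDB rate = 0.95 + 0.05f
- Decompression rate = 0.70 + 0.30f
- Difference = 0.25 - 0.25f = 0.25 x (1 - f)

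**Exact power at 37 per arm, same f in both arms.**

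| f | EDB | Decompression | Difference (points) | Pearson | Fisher |
|---|---|---|---|---|---|
| 0 | 95% | 70% | 25 | 86% | 78% |
| 10% | 95.5% | 73% | 22.5 | 82% | 70% |
| 20% | 96% | 76% | 20 | 77% | 62% |
| one third | 96.7% | 80% | 16.7 | 68% | 47% |

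**Ablation alone.** If one of 37 decompression participants is converted by ablation and no EDB participant is, the decompression rate is 0.70 + 1/37 = 72.7%. Power against 95% is then about 80% (Pearson) or 68% (Fisher).

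**Where f is likely to lie.** Three statements point to a low value:
- Section 5.3 reserves ablation for exceptional cases.
- Chapter 1 calls the effect of intratympanic steroids temporary.
- Section 4.2 admits only patients who have already responded insufficiently to at least two injection sessions.

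**The case against.** **The window is not defined.** The protocol nowhere says in words that rescued participants are successes, and it does not say what period attack freedom at 12 months covers. If it meant the whole follow-up year, anyone rescued for continuing attacks would already be a failure. This stands as a limit on certainty. The wording in 8.1.1 and 10.1 reads more naturally as status at 12 months, and no whole-year window is stated.

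**Counting outcomes regardless of later treatment is a recognised intention-to-treat strategy.** Section 5.3 defends shared decision-making as reflecting practice. That is a fair reason to report the attack-only result. It is a weaker reason to make it primary when one rescue option abolishes the function that EDB is meant to preserve. Nor is this a detail to leave to an analysis plan, because the protocol itself defines the endpoint and the place of rescue.

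**Rescue is not concealed.** It is recorded as a secondary parameter, and patient and follow-up surgeon are blinded (8.2.2), so an imbalance would be visible. That is correct, but it does not correct the primary comparison.

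**A much larger loss might be inferred.** Raising only the decompression rate while holding EDB at 95% gives 54%/36% (Pearson/Fisher) when one third of control failures are converted and 33%/16% when half are. That assumes no EDB failure is ever rescued. With equal conversion, half gives 54%/28%. The protocol's wording on rescue does not support fractions that high.

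**The 70% benchmark may already include later treatment.** It comes from cited studies, and the protocol does not say how they handled rescue. If their rates include it, adding f on top double counts. This cannot be settled from the protocol.

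**Conclusion.** The point holds as a gap in the endpoint definition. On the natural reading, ablation after a failed operation yields a primary success for that operation. If the planned rates hold, the bias is towards no difference, so it does not favour a false claim for EDB.

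The size is uncertain and probably modest: a few points of power for an isolated ablation or for f around 10%, and more only if rescue is common and effective. Fisher's test has no margin, since it is already below 80% at 37 per arm with no rescue.

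A reader might infer that the protocol states that rescued participants are successes, or that treatment failure is hidden almost only in the control arm. The protocol supports neither as fact. The first depends on the undefined window, and the second on the 95% v 70% alternative being true.

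The correction is worth making because it is cheap and settles what success means. It is not evidence that the design is unsound.

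**What to change.** In 8.1.1 and 10.1, define primary success as no attack in the 12-month window and no ablative procedure since study surgery. State the window, so that the rule has one reading.

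Pre-specify a sensitivity analysis that also scores any intratympanic injection after study surgery as failure, and report the attack-only version as supportive. Scoring ablation as failure removes only the ablation part of the loss. The effect of injections remains in the primary result, which is why the sensitivity analysis is needed.

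The cost is a few sentences. Section 8.1.2 already provides for recording ablation and injections, and when rescue is offered does not change. The downside is that the endpoint becomes a composite that includes a shared treatment decision. Because patient and follow-up surgeon are blinded, that decision should not favour either arm.

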## **6. INVESTIGATIONAL PRODUCT**

Not applicable.

## **7. NON-INVESTIGATIONAL PRODUCT**

Not applicable.

## 8. METHODS

### 8.1 Study parameters/endpoints

#### 8.1.1 Main study parameter

The main study parameter is the number of patients free of vertigo attacks at 12 months after surgery. This parameter was chosen because vertigo is the most invalidating symptom of MD.

#### 8.1.2 Secondary study parameters

- Cumulative incidence of vertigo bouts
- Hearing
  - As defined in the diagnostic criteria of the Bárány Society (Lopez-Escamez, 2016), the following parameters will be assessed based on a three-tone audiometry at 0.5, 1 and 2 kHz (LFI):
    - The three-tone average score in decibels (dB), labelled as hearing threshold (HT).
    - Word recognition (WR), based on the speech discrimination. A decrease of  $\geq 10$  dB or a change in word recognition score of  $\geq 15\%$  points is considered clinically significant. When the pure-tone average and the WR change in the opposite direction, the pure-tone average score will be decisive to conclude the overall nature of change in hearing.
  - All pure tone audiometry analyses will be executed by the participating centre itself.
- Use of escape medication
  - The frequency and use of escape medication in the acute phase of vertigo will be recorded. This includes intratympanic injections and antivertigo medication.
- Co-interventions
  - Co-intervention is defined as performed ablative surgery during the follow up period because of unbearable vertigo bouts.
- Complications of surgery
- Functional Level Scale (FLS)
  - To assess the effect of the vertigo attacks on daily life, the 6-point FLS is recommended by the AAO-HNS for clinical trials in MD (Committee on Hearing and Equilibrium guidelines for the diagnosis and evaluation of therapy in Ménière's disease, 1995). One value is chosen to score the level of disability. The score will be reported as a total score, as

well as categorized into improvement, unchanged or worsened.

Categories will be based on the following definitions:

- Improvement: one or more points decrease on the FLS score compared to the baseline FLS score
- Unchanged: unchanged FLS score compared to the baseline FLS score
- Worsened: one or more points increase on the FLS score compared to the baseline FLS score.

- Dizziness Handicap Index (DHI)

- To evaluate the effect of vertigo in the patient's daily life the 25-item measure of the DHI is used which was developed by Jacobson and Newman (1990). This inventory is often used for follow-up of participants suffering from dizziness. Higher scores indicate more severe handicap. According to a review published in 2007 (Duracinsky 2007) it is a valid tool and could be regarded as a questionnaire of reference.
- The outcome is categorized as following:
  - 0-16 points: no handicap
  - 16-34 points: mild handicap
  - 36-52 points: moderate handicap
  - 54+: severe handicap
- Categories will be based on the following definitions:
  - Improvement: the DHI score reflects at least 18 point improvement compared to baseline (Jacobson 1990).
  - Unchanged: the change in DHI score no greater than a 17 points increase of decrease compared at baseline.
  - Worsened: the DHI scores reflects a decrease of more than 17 points compared to baseline

- Tinnitus Handicap Index (THI)

- To quantify the effect of tinnitus on daily life, the THI is used. The scale is grouped into functional, emotional, and catastrophic subscales. According to literature, the THI is a reliable and valid tool for measuring the impact of tinnitus on the quality of life (Newman (1996)), Kleinstäuber (2014)). The Dutch version of the questionnaire that will be taken is validated (Vereeck L 2006) It uses the following grades of handicap due to tinnitus:
  - 0-16: Slight or no handicap (Grade 1)
  - 18-36: Mild handicap (Grade 2)
  - 38-56: Moderate handicap (Grade 3)

- 58-76: Severe handicap (Grade 4)
  - 78-100: Catastrophic handicap (Grade 5)
- Categories will be based on the following definitions:
  - Improvement: decrease in grade of THI at 6 and 12 compared to the baseline THI grade.
  - Unchanged: unchanged THI grade compared to the baseline THI grade.
  - Worsened: increase on the THI grade compared to the baseline THI grade.
- SF-36
  - The SF-36 encompasses eight health concepts: physical functioning, bodily pain, role limitations due to physical health problems, role limitations due to personal or emotional problems, emotional well-being, social functioning, energy/fatigue, and general health perceptions. It also includes an item that provides an indication of perceived change in health.

Scores are calibrated so that 50 is the average score or norm (Ware, 1993).
- EQ-5D VAS
  - The EQ-5D VAS records the respondent's self-rated health on a vertical, visual analogue scale where the endpoints are labelled 'best imaginable health state' and 'worst imaginable health state'.
- CEA
  - A trial-based cost-effectiveness analysis (costs per prevented vertigo-attack, from a healthcare perspective) and cost-utility analysis (costs per QALY, from a societal perspective), and cost-calculator spreadsheet model to estimate budget-impact from different perspectives will be performed using QALYs as the patient outcome. The EQ-5D and VAS score at 0, 3, 6 and 12 months will be used to assess quality of life.
- iPCQ
  - The productivity cost questionnaire (iPCQ) developed by Institute for Medical Technology Assessment (iMTA) assesses the impact of disease on the ability of a person to perform work. It is a standardized instrument for measuring productivity losses to enhance the comparability and generalizability of the outcomes of economic evaluations.
- iMCQ
  - The medical cost questionnaire (MCQ) developed by Institute for Medical Technology Assessment (iMTA) is used to measure health-care utilization. It

includes questions related to frequently occurring contacts with health care providers.

- BIA
  - Budget impact will be evaluated from the perspective of society, BKZ ('budgettaire kader zorg'), health insurer and the different specialists. The analysis will take into account the current mix of treatments with the annual number of procedures obtained from Vectis data.
- Endolymphatic hydrops and perilymph signal intensity on MRI
  - Recently developed MR-imaging allows visualization of perilymph signal intensity, and visualisation and grading of endolymphatic hydrops in the inner ear (Van Steekelenburg 2020). Hydrops is associated with duration of MD and saccular hydrops is associated with sensorineural hearing loss (Attyé 2018). Perilymphatic signal intensity is a surrogate marker for impaired blood-labyrinth permeability. Signal intensity (without) hydrops is markedly increased in the acute phase of labyrinthitis, and is increased in patients with MD (Shi, 2018). Overall, evidence is accumulating that both hydrops and signal intensity of the perilymph are associated with disease burden and may reflect disease activity. Therefore, we hypothesize that EDB results in a decrease in hydrops and perilymph signal intensity.
  - These two parameters will be measured pre-operatively, as well as 3-months and 12-months post-operatively to assess if the hydrops diminishes after EDB and is clinically relevant.
  - The protocol for the scans can be found in the appendix (Appendix 5)
- Physiotherapeutical outcomes
  - Balance
    - Assessment of static standing balance will be done by performing a Romberg, a sharpened Romberg and One Leg Stance Test. These tests are often used in the vestibular population (Gotshall 2011, Herdman 2014). Balance is a marker of vestibular function and it will be used as a guide in the vestibular rehabilitation. The results of the balance test will be compared with normative values (Gill-Body et al 2000, El Kashlan et al 1998)
    - The aim is to optimize balance ((sharpened) Romberg, one leg stance test), in which we strive to meet norm value or reaching a plateau for 6 weeks, within 3 months.
  - Gait

- Gait will be assessed using the dynamic gait index (DGI), an instrument to evaluate an individual's ability to modify balance during walking. This tool is a marker of vestibular function, as an intact VOR is required to perform the tests.
- The DGI contains 8 items which are all scored on a 4-point scale: 3 points for optimal score (no gait dysfunction), 2 points for minimal impairment, 1 point of moderate impairment and 0 points if there is a severe impairment in gait.
- Improvement in gait is defined as 4.0 points (Marchetti 2014) improvement on the total of 24 points possible, compared to baseline.
- Dynamic Visual Acuity
  - Dynamic Visual Acuity will be measured using DVAT-NI. DVAT-NI measures the gaze stability by assessing the vestibulo-ocular reflex (VOR) function in response to examiner generated rotational head movement stimuli (2 Hz) during reading lines of the ETDR chart (SLOAN). The DVAT-NI is used to screen and characterize the severity of gaze instability.
  - Patient with a score of two or more line difference between static and dynamic acuity is defined as having an abnormal DVA (Dannenbaum 2009). The DVAT-NI is a clinical used test and used as a guide to treatment (Dannenbaum 2005, Dannebaum 2009, Herdman 2014) and to treatment efficacy.

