#### **10.2.2 Computation of outcome**

All secondary outcomes will be analysed using a linear mixed model (EDB vs decompression group) at the different time measurement point.

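### The overall hearing label lets a pure-tone change of any size override a word-recognition change that the protocol itself calls clinically significant

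*Protocol*

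**What the plan says.** Protocol section 8.1.2 lists two hearing parameters. One is "The three-tone average score in decibels (dB), labelled as hearing threshold (HT"), averaged over 0.5, 1 and 2 kHz. The other is "Word recognition (WR), based on the speech discrimination".

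It then gives two rules in succession:

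- **Significance.** The limits are 10 dB for the threshold and 15 percentage points for WR. They are joined by 'or' ("dB or a change in word recognition score of" at least 15 points), so either suffices.
- **Tie-break.** "When the pure-tone average and the WR change in the opposite direction, the pure-tone average score will be decisive to conclude the overall nature of" (any shift in hearing).

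The tie-break does not say that either movement must be clinically significant, and no other section adds such a limit. Section 10.2.2 says only: "All secondary outcomes will be analysed using a linear mixed model (EDB vs decompression group) at the different time measurement point". For the Dizziness Handicap Inventory, by contrast, section 8.1.2 defines a band of scores that counts as unchanged. Hearing has no such band.

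**The concern.** The two rules do not fit together. The first lets a WR change of 15 points or more stand on its own. The second removes that status whenever the PTA has moved the other way, even by an amount that the first rule treats as not significant. Two patients with the same large WR change can then receive different overall labels because their PTAs differ by 2 or 3 dB, neither PTA change being near 10 dB.

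What is at stake is the overall hearing classification. Hearing is a stated secondary objective (section 2). The exclusion of patients deaf in the other ear is justified in section 4.3 by uncertainty about what duct blockage does to hearing. A label that turns on noise makes that comparison harder to read. The protocol fixes this rule itself, so an analysis plan that followed it literally would inherit the problem.

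**Working it through.** The protocol states no figure to reproduce here. The check has two parts: applying the rule as written, and gauging its size under assumed values.

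**1. The rule applied to worked cases**

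Inputs from section 8.1.2: limits of 10 dB and 15 points, and the tie-break with no minimum. I read opposite direction as opposite in meaning for hearing, and the 10 dB limit as a change either way. A negative PTA change means a better threshold. The last column requires both limits to be met before the PTA decides.

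| PTA change (dB) | WR change (points) | Rule as written | With both limits required |
|---|---|---|---|
| -12 | -20 | PTA decides; significant | PTA decides |
| -2 | -20 | PTA decides; below 10 dB, WR loss overridden | WR loss stands |
| -1 | -20 | PTA decides; below 10 dB, WR loss overridden | WR loss stands |
| 0 | -20 | No conflict; significant loss | WR loss stands |
| +1 | -20 | No conflict; significant loss | WR loss stands |
| +2 | -20 | No conflict; significant loss | WR loss stands |

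Take a patient whose WR falls from 80% to 55% (25 points). With PTA going from 50 to 51 dB this is a significant loss. With PTA going from 50 to 48 dB the PTA decides, and the result is not a loss. The rule is symmetric: a 25-point WR gain with the PTA 2 dB worse is overridden in the same way.

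**2. Possible size**

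The protocol gives no standard deviation (SD) or correlation, so these are assumptions: mean changes of zero; SD of PTA change 6 or 8 dB; SD of WR change 10 or 12 points; bivariate normal, rounded to whole units; correlation 0, -0.3 or -0.6 (negative because a higher threshold goes with lower WR). The arm size of 37 is from section 4.4.

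Overridden losses per arm = 37 × P(WR change ≤ -15 and PTA change from -9 to -1).

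The largest case can be done by hand (correlation 0, PTA SD 6, WR SD 12):

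- P(WR ≤ -15) = Φ(-14.5/12) = 0.1135
- P(PTA from -9 to -1) = Φ(-0.5/6) - Φ(-9.5/6) = 0.467 - 0.057 = 0.410
- 37 × 0.1135 × 0.410 = 1.72

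Simulation over all four SD combinations (2,000,000 draws each) gives:

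| Correlation | Overridden WR losses per arm | Share of all WR losses of 15 points or more |
|---|---|---|
| 0 | 1.0 to 1.7 | 36% to 41% |
| -0.3 | 0.6 to 1.1 | 22% to 26% |
| -0.6 | 0.2 to 0.4 | 7% to 9% |

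Overridden WR gains come out at the same numbers, as they must with zero mean change. The counts are for one comparison with baseline; section 8.3.3 schedules audiometry at 3, 6 and 12 months.

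**3. If the PTA truly worsens among patients with a WR loss**

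The chance of a small move in the better direction is Φ((0 - m)/s) - Φ((-10 - m)/s), with m the mean worsening and s the SD. For m = 0 and s = 3, 5, 7 dB it is 50%, 48% and 42%. For m = 5 dB it is 5%, 16% and 22%. For example, at s = 7: Φ(-0.714) - Φ(-2.143) = 0.238 - 0.016 = 0.221.

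**The case against.** The best defence is that the two sentences belong together. The first defines which changes count, so the change in the second may mean a change of that kind. On that reading the rule is sound and lacks only a clarifying word. The reading is possible, but the text does not state it, and an analyst who codes the sentence as written will get the literal result. The defence therefore supports the rewording.

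The hearing parameters are also said to follow a cited consensus document. Whether the tie-break comes from there, and whether rewording would cost comparability, cannot be judged from the protocol.

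Three stronger conclusions that a reader might draw are not supported:

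- **That WR losses disappear from the trial, or that deterioration is systematically under-counted.** Threshold and WR are listed as separate parameters, and nothing makes the overall label the only hearing comparison. The override also cancels gains as well as losses.
- **That hearing safety is compromised.** Hearing loss is listed among the surgical risks, with all adverse events recorded (section 9.2.1). Permanent hearing loss is named among the events counted for notifying the ethics committee (section 9.1), and severe hearing loss from surgical damage is a ground for considering termination (sections 8.7 and 9.5). None of these refers to the tie-break.
- **That the rule never fires in a true conflict, because a worse threshold is a higher number and a worse WR a lower one.** This needs direction to be read off the raw numbers. The sentence is about change in hearing, so opposite effect on hearing is the natural meaning, and it is the meaning under which the 50 to 48 dB example is overridden at all.

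**Conclusion.** The point holds as a defect in a stated rule of limited reach. As written, a PTA change below the protocol's own 10 dB limit can override a WR change that meets the 15-point limit, in either direction, so the overall hearing label can turn on audiometric noise.

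Its size in this trial cannot be known from the protocol. The range of 0.2 to 1.7 overridden WR losses per arm of 37, with about as many gains, rests wholly on assumed SDs and correlations and on zero mean change. The upper end requires two hearing measures on the same ear to be uncorrelated, so it should not be taken as the expected value. If the PTA tends to worsen alongside WR, overridden losses become fewer.

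The primary endpoint and the sample size are untouched. This is a minor correction worth making.

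**What to change.** Replace the tie-break sentence in section 8.1.2 with:

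> If PTA (at least 10 dB) and WR (at least 15 points) both change by a clinically significant amount, one showing better and the other worse hearing, the PTA decides. If only one reaches its threshold, that one decides.

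This uses the protocol's own limits, keeps the PTA's priority in a genuine conflict, and states direction in terms of better or worse hearing. It costs one sentence and needs no new data, visits or tests. It should be settled before unblinding and carried unchanged into the analysis plan.
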